### Economic analysis

The economic analysis of the intervention will focus on a cost-effectiveness and a cost-benefit analysis. The implemented intervention and the usual care will be compared in each of these analyses.

The cost-effectiveness analysis (CEA) will compare the relative costs invested and effects of implemented intervention and usual care. On the other hand, the cost-benefit analysis will indicate the savings per dollar invested in the implemented intervention in terms of the benefit/cost ratio. Benefits will be assessed by assigning a monetary value to the effects. Because of the ethical and methodological problems in the assignment of a monetary value to quality of life, morbidity and mortality [77,78], the cost-benefit analysis will be based on a pragmatic approach; it will focus on the savings gained in relation to the reduction of health care use due to the implemented intervention.

### Stages of data acquisition and analysis

(1) **Cost analysis**. Cost analysis will be performed from an organizational perspective; that is, only costs related to the FMG and CSSS will be outlined. The costs of the intervention and of usual care will be identified. For the experimental group, the average nurse’s salary for the time devoted to intervention will be obtained (average cost per patient). The data on services obtained from the CSSS (emergency visits, hospitalizations, etc.) and from the FMG (excluding management of cases already included in the calculation) during the six-month follow-up will also be obtained and their monetary value will be estimated, using the average cost per patient for both groups. (2) **Measurement of effectiveness**. Data collected as part of the impact evaluation (intermediate outcomes) will be used to document the effects of the intervention on empowerment, quality of life, and use of services (emergency visits, hospitalizations, other CSSS services and FMG services). The effects will be measured in terms of the empowerment gained, quality of life gained, and, the reduction in use of services. (3) **Efficiency analysis**. Costs and effects will be compared, in order to identify whether the intervention or the usual care leads to better effectiveness at lower cost. Incremental cost-effectiveness ratios (ICER = Δ Effectiveness/Δ Costs) will be calculated. This component will address the following three questions: (1) How much does it cost to improve empowerment? (2) How much does it cost to improve quality of life? (3) How much does it cost to decrease use of CSSS or FMG services? (4) **Cost-benefit analysis**. A cost-benefit analysis will be performed if a reduction in the use of services is documented (see power calculation in “sample size and statistical power” section presented previously). The cost differential of the cost of services avoided, related to a reduction in the use of services for the number of patients surveyed (Δ benefits), will be compared to the cost differential of the intervention and the usual care (Δ costs) so as to assess whether the new intervention is cost-effective. We will calculate the gain per dollar invested in the intervention by estimating the Δ benefit/Δ cost ratio. If this ratio is greater than 1, a gain will be indicated; otherwise, a break-even point will be estimated by evaluating the minimum cost at which the intervention will become cost-effective. This analysis would also estimate the caseload for obtaining a break-even point and for identifying the profile of patients for whom the intervention was more cost-effective. (5) **Sensitivity analysis**. Since many uncertainties are generally present in the economic and effectiveness data, it will be important to complete the analysis by: (1) identifying and explaining the sources of uncertainty; and (2) performing sensitivity analyses by varying the value of specific parameters related to the sources of uncertainty, in order to assess the robustness of outcomes [77,79], and if necessary, to determine the break-even point of the intervention.

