#### Study population

Targeted patients will be those described in the objectives. The concept of vulnerability will be operationalized by considering both the frequency of the CSSS care use (emergency room visits and hospitalization) and patient vulnerability characteristics, based on the judgment of the primary care team in the FMG. This combined approach was proposed as a more favourable strategy for patient identification for this kind of intervention, when compared to using each one of these strategies in isolation [57]. Steps to target the most vulnerable participants will include: 1) Presentation of the intervention to FMG primary care physicians and nurses, 2) Delivery of a computerized list (obtained using MAGIC Chronique software by MédiaMed Technologies [58]) of the 300 most frequent users of CSSS services (emergency department visits and hospitalizations) having at least one of the targeted CD in each FMG. FMG professionals will then identify the 100 patients they believe will benefit most from the intervention described. The software used for patient identification will serve as a system to support decision-making for primary care teams who did not have access to this kind of information up till now.

After verifying patient eligibility and obtaining their consent, participants will be allocated to one of two groups (experimental or control) according to a three-stage randomization process [59]: (1) generation of the patient allocation sequence using a simple randomization procedure; (2) allocation blinding (sequentially numbered and sealed in opaque envelopes); (3) assignment of participants by opening the envelopes at the time of recruitment. The experimental group will consist of a sample of 50 patients in each of the four FMG (n = 200). These patients will receive the intervention for six months. Patients in the control group (n = 200) will receive the usual care for six months and then the same intervention as the treatment group for the following six months (waiting list control group) [60]. This is intended to avoid the problem of demoralization of the control group, in addition to ensuring fair treatment among participants in both groups.

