### Measures

The variables defined within the logic model will be measured using instruments that are well known and have been validated in studies similar to the one proposed.

The proximal outcomes, evaluated at T0 (recruitment period), T1 (3 months) and T2 (6 months) for both groups (see Table 2), will be: (1) self-efficacy measured with the *Self-Efficacy for Managing Chronic Disease* scale [61]; (2) self-management practices, with the *Self-monitoring and Insight* sub-scale of the *health education impact questionnaire* (heiQ [62,63]; (3) health habits, using the questionnaire developed as part of the PRECISE study [64]; (4) patient activation, with the *Patient Activation Measure*[65]; and (5) psychological distress, with the *Psychological Distress Scale*[66].

**Table 2 T2:** Proposed study plan

	**Visit 1**	**Visit 2**^**1**^	**Visit 3**	**Visit 4**	**T3**^**2**^
	**T0**		**T1**	**T2**	
Time from the start of the intervention	−2 weeks	0	3 months	6 months	12 months
Verification of eligibility	√				
Informed consent	√				
Covariables: Socioeconomic level, social isolation, literacy, mental health and multimorbidity	√				
Proximal outcomes: Personal self-efficacy, self-management practices, lifestyles, activation and psychological distress	√		√	√	
Intermediate outcomes: Empowerment, quality of life and use of services	√			√	√

^1^ Visit 2 will mark the beginning of the intervention. This will be two weeks after randomization for the experimental group and 6 months after randomization for the control group.

^2^ For the experimental group and use of services only.

Intermediate outcomes, evaluated at T0 and T2 (see Table 2), will include: (1) empowerment, measured with the heiQ scale [62]; (2) quality of life, measured with the SF-12v2 scale [67]; and (3) the use of health services, measured using clinical data from the CSSS (with Magic Chronique software by MediaMed) for hospitalizations, emergency room visits and CSSS services (e.g., psychosocial services or specialized services related to the specific CD), and electronic data on visits with physicians and nurses in the FMG.

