#### Sample size and statistical power

When analyzing quantitative data, we must take into account that part of the effect is potentially associated with each of the eight case management nurses. The intra-nurse or intracluster correlation (ρ) is unknown, however, and is specific to each variable. On the other hand, given that series of standardization measures will be implemented to minimize nurse-specific effects, we anticipate that the intracluster correlation will not be higher than 0.10. Sample size was therefore calculated using this maximal anticipated ρ-value. Results indicated that a standardized effect size (ES) of 0.5 (qualified as medium [73]) will be detectable with two groups of 200 participants (25 per nurse) for a two-tailed test with the α level set at 0.05 and a power of 80% [74]. An ES of at least this magnitude can be expected since it was observed in a previous study [75] and in unpublished data from the CSSS de Chicoutimi. An ES of at least 0.5 also represents the clinically significant effect needed to justify the pragmatic integration of the intervention into the services already provided. For example, in the case of patient empowerment, the ability to detect an ES of 0.5 translates into the capacity to detect any difference of at least half a point within different domains of the heiQ, since the overall standard deviation is about 1 point [76]. The detection of smaller differences is irrelevant since it is not clinically significant.

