### Data analysis plan

All statistical analyses will be performed based on an intent-to-treat principle. We will first describe the characteristics of participants in each group, using means and standard deviations (continuous variables) or percentages (categorical variables). The groups will be compared at baseline (T0) using Student’s T test or the Chi-square test. Wherever possible, comparisons will be made between patients who agreed to participate in either phase of the study and those who refused, in order to document biases related to refusals. For outcome indicators at 3 months (self-efficacy, self-management practices, health habits, activation and psychological distress), groups will be compared at T1 using analysis of covariance adjusted for T0 scores. For indicators measured at six months (empowerment, quality of life and use of care), repeated measures analysis of variance will compare change over time in the two groups. In all cases, if the groups initially differ with regard to certain characteristics despite randomization, analysis will be adjusted to take into account the relevant variables. In addition, if a nurse effect is present (non-null intracluster correlation), despite efforts at standardization, multi-level analysis will be conducted to take this into account.

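### Service costs are compared on six-month follow-up averages alone, without the T0 service use the trial collects, so Δ costs in the ICER is less precise than the data allow

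*Protocol article*

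**What the plan says.** Four parts of the protocol article bear on this.

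- **Stages of data acquisition and analysis, stage (1).** Data on services from the CSSS and the FMG "during the six-month follow-up will also be obtained and their monetary value will be estimated, using the average cost per patient for both groups". The window is follow-up only, and no T0 quantity is named.
- **Measures, and Table 2.** "Intermediate outcomes, evaluated at T0 and T2 (see Table 2), will include" use of health services, taken from CSSS clinical data and FMG electronic data. These are the sources that stage (1) costs.
- **Data analysis plan.** For the six-month indicators, use of care among them, "repeated measures analysis of variance will compare change over time in the two groups". T0 therefore counts when use itself is analysed. The section adds that "if the groups initially differ with regard to certain characteristics despite randomization, analysis will be adjusted to take into account the relevant variables".
- **Study population.** Patients come from lists of the 300 most frequent users in each FMG. Allocation rests on "generation of the patient allocation sequence using a simple randomization procedure", and no balancing on prior use is stated.

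Stage (2) takes the effects from the impact evaluation, expressed as gains or reductions. Stage (4) ties Δ benefits to the reduction in use, and describes Δ costs as the difference in cost between the intervention and usual care.

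**The concern.** The same visits and admissions are handled in two ways. As an effect, use of care is analysed with T0 taken into account. As a cost, it enters as a follow-up average without T0. The third ICER question, on the cost of decreasing use of services, puts both treatments into one ratio.

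Past use is a plausible predictor of later service cost. Under simple randomization one group may by chance start with heavier users. Part of that difference would then show up in the follow-up averages and be read as a cost or saving of the intervention. The cost comparison would also be less precise than the collected data permit. The Discussion says that the economic results will inform decision-makers on resources, so the precision of Δ costs matters.

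**Working it through.** **No cost figure to reproduce.** The plan states no cost SD, cost difference or correlation. Its one calculation is the sample size, from which only the group size is used here: "two groups of 200 participants (25 per nurse) for a two-tailed test with the α level set at 0.05 and a power of 80" per cent. That calculation is a separate matter and nothing below depends on it.

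**Inputs.** n = 200 per group (Sample size and statistical power). Assumed: r = 0.3, 0.5, 0.7; equal cost SD at T0 and follow-up; coefficient of variation (CV, SD divided by mean) of 1 to 2. Clustering is set aside until the last step.

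**Formulas, in units of the cost SD.**
- Follow-up averages: SE = √(2/200) = 0.100.
- Regression on group and T0 cost: SE = 0.100 × √(1 − r²).
- Change from T0: SE = 0.100 × √(2(1 − r)).

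| r | Follow-up averages | Regression on T0 | Variance cut by regression (r²) | Change score |
|---|---|---|---|---|
| 0.3 | 0.100 | 0.095 | 9% | 0.118 |
| 0.5 | 0.100 | 0.087 | 25% | 0.100 |
| 0.7 | 0.100 | 0.071 | 49% | 0.077 |

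Below r = 0.5 a change score is worse than ignoring T0. Regression is never worse by these formulas.

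**Carry-over of a chance imbalance.** The 95% range of the T0 difference in mean cost is 1.96 × CV × 0.100, or ±19.6% of mean cost at CV 1 and ±39.2% at CV 2. A fraction r carries over. At r = 0.5 that is 9.8% to 19.6% of mean cost at the edge of the range. An imbalance of one SE (0.10 SD) carries 0.03, 0.05 and 0.07 SD at the three values of r.

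**Simulation with skewed costs.** Log-normal costs, log-scale SD 1.2, 200 per group, 4,000 runs for each r, where r is the correlation on the log scale.
- Mean error of the unadjusted difference: under 0.4% of mean cost, so no bias.
- SD of the difference as a share of mean cost, unadjusted and then adjusted: 18.16% and 17.89% (r = 0.3); 18.36% and 17.19% (0.5); 17.81% and 14.58% (0.7).
- Variance cuts: 1 − (17.89/18.16)² = 3%; 1 − (17.19/18.36)² = 12%; 1 − (14.58/17.81)² = 33%.
- Slope of the follow-up difference on the T0 difference: 0.15, 0.33 and 0.55. A 1.96-SE imbalance (1.96 × about 18% = 35% of mean cost) then moves Δ costs by about 5%, 12% and 19% of mean cost.

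The smaller gains do not contradict the table. Skewness makes the correlation on the cost scale lower than on the log scale, and the squared slopes (2%, 11%, 30%) are close to the simulated cuts.

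**Clustering.** The plan says "we anticipate that the intracluster correlation will not be higher than 0.10", though not for costs specifically. With ρ = 0.10 and 8 nurses per group, the per-group variance is 0.10/8 + 0.90/200 = 0.0170. If T0 cost at r = 0.5 explains only patient-level variance, this becomes 0.10/8 + 0.65/200 = 0.01575, a cut of 7%. If it explains both levels alike, the cut stays at 25%.

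**The case against.** **Stage (1) may only describe data handling.** It says which data are obtained and how they are valued, it does not rule out adjustment, and an article may leave the cost model to a fuller plan. This stands in part. But the text does name a window and a summary for each group, and T0 is in neither.

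**The adjustment clause may already cover it.** The Data analysis plan applies the clause to all cases, and heavier users in one group are the kind of difference it addresses. This is why it would be too strong to say that the plan ignores baseline. The clause does not settle the matter, however. It depends on an observed difference, it stands in the effects section before the economic analysis, and it is not repeated there. If the T0 tests act as the trigger, imbalances short of significance go unadjusted.

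**The gain may be small.** Taking patients only from the heaviest users narrows the range of prior use and would tend to lower r. At low r the gain is slight. This stands.

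**Stronger readings that a reader might infer.**
- *That a baseline imbalance biases Δ costs or passes into it in full.* Randomization leaves the unadjusted difference unbiased on average, and only a fraction of about r carries over.
- *That the two sides of the ICER become incoherent.* Under randomization the unadjusted and adjusted differences target the same quantity.
- *That the benefit/cost ratio and break-even point rest on unadjusted follow-up costs.* Δ benefits is tied to the reduction in use, which comes from the effects evaluation. Only Δ costs could be exposed, and only if it includes stage (1) service costs, which stage (4) leaves open.

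**Conclusion.** The point holds in limited form. As written, the service-cost comparison leaves out a baseline measure that the trial collects and uses elsewhere for the same data. The consequence is avoidable imprecision and sensitivity to chance imbalance in the service-cost part of the ICER's Δ costs, not bias. The benefit/cost ratio is touched only to the extent that its Δ costs takes in those service costs.

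The size rests on assumed values of r and CV and cannot be fixed from the documents. The variance cut runs from 9% to 49% for r of 0.3 to 0.7 on the cost scale, and from about 3% to 33% when those correlations apply on the log scale. It is smaller still if nurses differ in cost and T0 use explains only patient-level variation. This is a low-cost improvement worth making before the data are analysed. It does not invalidate the economic analysis.

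**What to change.** Add to stage (1) that the between-group difference in service cost will be estimated by regressing follow-up service cost on group and T0 service use or cost, whatever the baseline tests show. Further points to state:

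- **Model.** It should suit skewed costs and allow zeros, for example linear regression with bootstrap intervals, or a two-part model with the group difference averaged over all patients. A plain gamma model cannot take zero costs. A change score should not be used.
- **Use.** The adjusted difference enters the ICER, and the benefit/cost ratio wherever stage (1) service costs form part of it. Stage (4) should say whether they do.
- **T0 window.** Neither Measures nor Table 2 defines a look-back period. Define one before randomization from the CSSS and FMG records, ideally six months to match follow-up, and value it with the same unit costs.
- **Reporting.** Show the unadjusted averages alongside.

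The cost is a short addition and one model. The team must confirm that records for the chosen T0 window can be extracted, since the article does not say so. The one analytic drawback is that Δ costs becomes model-based and is no longer a simple difference of two averages.

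### The ICER is written upside down, and the benefit/cost ratio has an ambiguous denominator, a one-directional trigger and a mislabelled break-even bound

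*Protocol article*

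**What the plan says.** All of the text is in the protocol article, under Economic analysis and Stages of data acquisition and analysis.

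- **Stage (1), cost analysis.** Nurse salary for intervention time is costed for the experimental group. Services from the health centres and the practices over six months are also collected, and "their monetary value will be estimated, using the average cost per patient for both groups". No other cost of usual care is itemised.
- **Stage (3), efficiency.** "Incremental cost-effectiveness ratios (ICER = Δ Effectiveness/Δ Costs) will be calculated". Three questions follow. The first is "How much does it cost to improve empowerment"; the others ask the same about quality of life and about reducing service use.
- **Stage (4), cost-benefit.** "A cost-benefit analysis will be performed if a reduction in the use of services is documented", with a pointer to the power section. The value of services avoided (Δ benefits) is set against the "cost differential of the intervention and the usual care (Δ costs"). A ratio above 1 counts as a gain. Otherwise "a break-even point will be estimated by evaluating the minimum cost at which the intervention will become cost-effective".
- **Stated aim of the ratio.** Both Economic analysis and stage (4) describe it as the return on each dollar put into the intervention.
- **Status.** Objectives and Economic analysis present the cost-benefit analysis without any condition.

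**The concern.** Economic analysis is one of the trial's three objectives, and the Discussion says the cost-benefit findings will inform decisions on staff and funding. Four statements in one section get in the way of that.

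1. The ICER formula does not give the quantity its questions ask for.
2. Δ costs in stage (4) can be read in two ways, and the ratio-above-1 rule gives opposite answers under the two readings over a wide range of results.
3. The ratio is produced only when service use has been seen to fall, so the savings that enter it are a favourable selection.
4. The break-even cost is described as the wrong kind of bound.

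The article states each of these, so none is a detail left to a fuller document.

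**Working it through.** The article gives no ICER, benefit/cost ratio or unit cost, so there is no economic figure to reproduce. Dollar amounts below are assumptions for illustration.

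**1. Direction of the ICER.** The formula has units of effect per dollar; the questions need dollars per unit of effect. Take ΔE = 0.5 heiQ point (the difference that Sample size and statistical power treats as clinically relevant) and assume ΔC = $600.

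- As stated: 0.5/600 = 0.00083 point per dollar.
- As the question requires: 600/0.5 = $1,200 per point.

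**2. What Δ costs contains.** Per patient, let I be the cost of delivering the intervention and S the service cost in the control group minus that in the experimental group.

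- Reading A, all stage (1) costs: Δ costs = (I + experimental services) − control services = I − S. The ratio is S/(I−S).
- Reading B, delivery cost only: Δ costs = I. The ratio is S/I.

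Reading A has literal support, because without services the usual-care side of the difference has nothing itemised in it. Reading B fits the stated return per dollar put into the intervention. S/I exceeds 1 exactly when S > I. S/(I−S) exceeds 1 when I/2 < S < I, is undefined at S = I, and is negative when S > I. With an assumed I = $1,000:

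| S | Net result S − I | S/I | S/(I−S) |
|---|---|---|---|
| 400 | −600 | 0.40 | 0.67 |
| 500 | −500 | 0.50 | 1.00 |
| 600 | −400 | 0.60 | 1.50 |
| 900 | −100 | 0.90 | 9.00 |
| 1,000 | 0 | 1.00 | undefined |
| 1,200 | +200 | 1.20 | −6.00 |

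The last column applies only under reading A. There, S = 600 would be called a gain although $400 is lost, and S = 1,200 would be called no gain although $200 is saved.

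**3. The trigger.** The article does not define what counts as a documented reduction.

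- If it means any observed fall: with no true effect and a symmetric estimate, about half of trials would open the analysis, all of them with S > 0.
- If it means a statistically significant fall: inputs from the sample size section are 200 per group, 25 per nurse, ρ = 0.10 and two-sided α = 0.05. The design effect is 1 + (25 − 1) × 0.10 = 3.4. With clustering in both arms, the standard error of a standardized difference is √(2 × 3.4/200) = 0.184, so only estimated reductions of at least 1.96 × 0.184 = 0.36 SD qualify. With clustering in the experimental arm only, it is √(3.4/200 + 1/200) = 0.148, and the cut-off is 1.96 × 0.148 = 0.29 SD.

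Chance of opening the analysis, Φ(ES/SE − 1.96):

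| True effect size | Both arms clustered | Experimental arm only |
|---|---|---|
| 0.2 | 19% | 27% |
| 0.3 | 37% | 52.5% |
| 0.4 | 58% | 77% |
| 0.5 | 77% | 92% |

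The last row compares with the article's stated 80% at 0.5; the point does not depend on that difference.

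**4. Break-even.** Hold S fixed. The ratio S/I reaches 1 when I = S and exceeds 1 only when I < S. With S = $600, the intervention pays only if delivery costs less than $600 per patient. The break-even value is therefore a ceiling on cost.

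**The case against.** **The double count.** A reader might conclude that the plan does count savings on both sides. The text does not establish this. No sentence puts services into the stage (4) denominator, and the aim is twice described as return on dollars put into the intervention, which is S/I. The ratio-above-1 rule also makes sense only under S/I. This objection stands: reading A cannot be presented as what the plan does. What remains is that stage (4) does not say what Δ costs contains, and that stage (1) leaves usual care with no itemised cost except services. Stage (1) does keep case management already counted out of practice services, but that guards against a different overlap.

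**The third ICER question.** A reader might see the same overlap in the cost of reducing service use. That is not an error. Net cost per event avoided is a legitimate quantity, with the effect counted in events and the cost in dollars.

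**The trigger.** It is a fall in use and not a favourable ratio. Once opened, a ratio of 1 or less leads to a break-even estimate, and the cost-effectiveness analysis carries no condition. It would therefore be wrong to say that only favourable cost-benefit results can be reported. It may also be argued that without a fall there are no savings to value. But S/I is well defined for zero or negative S as long as I is positive, and it then correctly shows no gain. Selection on the estimated saving remains.

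**Small matters of wording.** The ICER as stated is a reciprocal, and the questions beside it reveal the intent; the break-even number is the same under either label. Both are true, and both are reasons why the correction is easy. A method for confidence intervals is detail that an article may leave to the full plan.

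**Conclusion.** The point holds in four parts of different strength.

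- **ICER.** Wrong as written: it is the reciprocal of what its own questions require. This rests on no assumption.
- **Denominator.** Ambiguous. One literal reading gives S/(I−S), which would misclassify every saving between I/2 and I as a gain and every saving above I as no gain. The dollar examples hold only under that reading and an assumed I.
- **Trigger.** Conditioning on a fall in service use selects favourable savings estimates and conflicts with the unconditional description in Objectives and Economic analysis. If significance is meant, a true effect of 0.3 would open the analysis in 37% to 52.5% of trials. Those figures assume a normal approximation and the article's ρ of 0.10.
- **Break-even.** The bound is a maximum, not a minimum.

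Randomisation, the clinical outcome analyses and data collection are unaffected.

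**What to change.** Reword Stages of data acquisition and analysis as follows.

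1. Define ICER = Δ Costs/Δ Effectiveness.
2. In stage (4), state that Δ costs is the incremental cost of delivering the intervention only, and that all differences in service use enter Δ benefits. A separate symbol from the one in stage (3) would prevent confusion.
3. Run the cost-benefit analysis whatever the direction or significance of the service-use result.
4. At break-even, replace minimum cost with maximum cost, and note that no positive cost breaks even if there are no savings.

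The cost is a few sentences in one section. The inputs are already to be collected under stage (1), so no new data are needed.

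### The economic gain is read off a point ratio above 1; the gate before it is undefined and tests saving above zero, not saving above cost

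*Protocol article*

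**What the plan says.** All of this is in the protocol article, mostly under Stages of data acquisition and analysis.

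- **Gate.** "A cost-benefit analysis will be performed if a reduction in the use of services is documented", followed by a pointer: "see power calculation in “sample size and statistical power” section presented previously". The section pointed to uses a two-tailed test at α 0.05 with 80% power. What counts as documented is not stated.
- **Estimate.** "We will calculate the gain per dollar invested in the intervention by estimating the Δ benefit/Δ cost ratio".
- **Decision rule.** "If this ratio is greater than 1, a gain will be indicated"; otherwise a break-even point is estimated.
- **Uncertainty.** Step (5) has two parts: "identifying and explaining the sources of uncertainty", and then "performing sensitivity analyses by varying the value of specific parameters related to the sources of uncertainty", in order to judge robustness. The ranges, and whether the variation is deterministic or probabilistic, are not given.
- **Test of service use.** Under Data analysis plan, for the six-month indicators including use of care, "repeated measures analysis of variance will compare change over time in the two groups", with multi-level analysis if a nurse effect is present. No comparison is stated there for cost, net benefit or the ratio.

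**The concern.** Service costs and savings come from patient-level records in two groups of 200, with up to eight nurses adding a cluster effect. Service costs of frequent hospital users are likely to be skewed, so a few admissions can move the mean difference. A rule that reads a gain from the point ratio takes no account of that movement. Varying unit prices or nurse time shows how the ratio responds to those inputs, but need not show how far it would move in another sample of patients.

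The consequence is practical. The Discussion says that the caseload giving the best cost-benefit will inform decision-makers about resources. The same analysis is to yield a break-even caseload and a profile of the patients for whom the intervention pays best. A ratio slightly above 1 could come from an intervention that does not pay for itself.

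**Working it through.** **The plan's own figures.** The ratio threshold has no calculated figure behind it to reproduce. The gate points to the power calculation: effect size 0.5, 200 per group, 25 per nurse, intracluster correlation up to 0.10. The design effect is 1 + (25 − 1) × 0.10 = 3.4. With clustering in both groups, the detectable effect at 80% power is (1.960 + 0.842) × √(2 × 3.4/200) = 0.517, which rounds to 0.5; power at exactly 0.5 is 77.4%. The small shortfall does not bear on this point. The calculation matters here only because it supplies the standard errors.

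**Standard error of the difference in mean service cost, in SDs per patient.**
- Independent patients: √(2/200) = 0.100
- Clustering in the experimental group only: √(3.4/200 + 1/200) = 0.148
- Clustering in both groups: √(2 × 3.4/200) = 0.184

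**Assumptions.** Let c be the net intervention cost per patient in SDs of six-month service cost, taken as known, and R the true benefit/cost ratio. The document gives no cost SD, unit cost or intervention cost, so c is varied from 0.05 to 0.5. The estimated saving is taken as Normal(R·c, SE), and service use and its cost are treated as one scale.

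**Formulas.**
- Ungated: P(ratio > 1) = 1 − Φ((c − R·c)/SE)
- Gate read as two-sided p<0.05 for a reduction: replace the first c in the bracket by max(c, 1.96·SE)

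**Example.** With c = 0.10, R = 0 and SE = 0.10, the ungated value is 1 − Φ(1.00) = 15.9%. The gated value is 1 − Φ(1.96) = 2.5%.

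| True ratio R | c | SE | Ungated | Gated |
|---|---|---|---|---|
| 0 | 0.05 | 0.100 | 30.9% | 2.5% |
| 0 | 0.10 | 0.100 | 15.9% | 2.5% |
| 0 | 0.30 | 0.100 | 0.1% | 0.1% |
| 0.5 | 0.05 | 0.100 | 40.1% | 4.4% |
| 0.5 | 0.10 | 0.100 | 30.9% | 7.2% |
| 0.5 | 0.30 | 0.100 | 6.7% | 6.7% |
| 1 | 0.05 | 0.184 | 50% | 4.6% |
| 1 | 0.10 | 0.100 | 50% | 16.9% |
| 1 | 0.20 | 0.184 | 50% | 19.1% |
| 1 | 0.20 | 0.100 | 50% | 50% |
| 1 | 0.50 | 0.184 | 50% | 50% |

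**What the gate does to the estimate.** A significant reduction must exceed 1.96·SE, which is 0.196, 0.291 or 0.361 SD for the three standard errors. If c lies below that value, every analysis that passes the gate returns a ratio above 1, whatever the truth, so the ratio rule adds no information.

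The mean reported ratio given a pass is [R·c + SE·φ(z)/(1 − Φ(z))]/c, with z = (1.96·SE − R·c)/SE. At true break-even (R = 1):
- c = 0.10: 2.49 with SE 0.100, and 4.45 with SE 0.184
- c = 0.20: 1.39 with SE 0.100, and 2.31 with SE 0.184

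**If the gate means only an observed reduction,** it adds nothing. With a positive net cost, a ratio above 1 already requires one, and the ungated column applies.

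**The case against.** The strongest reply is the gate. A reader might infer from the ratio rule that sampling error is ignored, or that the rule as written gives a wrong answer at a high rate. The article does not support either reading. The ratio is reached only after a reduction in service use has been documented, with a pointer to a two-tailed 0.05 calculation, and service use is tested between the groups. If the gate is that test, a gain from no saving at all is held to 2.5%. With cost 0.05–0.10 SD and SE 0.10, a gain at a true ratio of 0.5 falls to 4–7%. This stands.

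Three further replies have weight:
- Step (5) also commits to explaining the sources of uncertainty in the effectiveness data. Its wording does not restrict it to one-way or deterministic variation, so varying the effect over its confidence limits would fit. It does not require that either.
- The article is condensed, and a full analysis plan may specify intervals or bootstrapping. Their absence is not the point here. The point is a rule that is stated, and stated on the point estimate.
- The efficiency step, which asks "in order to identify whether the intervention or the usual care leads to better effectiveness at lower cost", gives a purpose and no threshold, so it is not evidence of a faulty rule.

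The reply does not settle what documented means. Nor does it change the fact that a test of saving above zero says nothing about saving above cost.

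**Conclusion.** The point holds in limited form. The stated rule indicates a gain from the point ratio, and the uncertainty step attached to it need not reflect sampling variation or clustering. The gate protects well against a gain from no saving, if it is a significance test. It does not protect near break-even, where a chance gain occurs in about 5% to 50% of trials depending on cost and standard error, and where the ratio that passes the gate is too large on average.

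The 16–31% rates for no saving apply only if the gate is not a significance test and the cost is 0.05–0.10 SD. At 0.30 SD with SE 0.10 the ungated rate is already 0.1%. All these sizes rest on assumed costs, on a normal approximation, on a known intervention cost, and on treating service use and service cost as one scale. They show the behaviour of the rule and do not predict this trial's result.

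**What to change.** 1. Define documented: name the service-use measure, the test and the level, or state that any observed reduction qualifies.
2. Bootstrap patients within group, and nurses in the experimental group, keeping each patient's cost and effect together.
3. Report 95% intervals for Δcost, Δeffect and net benefit (savings minus intervention cost), with the probability that net benefit exceeds zero.
4. Word the gain statement with that interval and probability instead of the point ratio alone. Whether a gain should also require the interval to exclude zero is debatable and need not be imposed.
5. Keep the parameter-variation analyses as an addition.

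The cost is a little extra programming on data already collected, and a less decisive economic statement.
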